## D. Research Design and Methods

This will be a randomized trial in which we will compare changes in screening, diagnosis, and management of ASD before and after implementation of the CHICA system in intervention control practices. Although the unit of randomization will be the primary care practice, the unit of analysis will be the individual patient.

Currently, CHICA is being utilized within a purely academic setting. However, by the start of this research project, CHICA will have expanded into the community practice setting through its incorporation into pediatric clinics in the Indianapolis area that participate in the Indiana University Medical Group – Primary Care (IUMG-PC) practice network. IUMG-PC includes 14 clinic sites that cater to pediatric patients. In 2007, these clinics hosted 95,011 patient visits for children between the ages of 0 and 13. 24% of these visits were for pediatric patients with Medicaid.

For this study, we will be focusing on four of the pediatric IUMG-PC clinics that have been previously set up with the CHICA system. These four clinics see the largest number of pediatric patients within the IUMG-PC practice network. For example in 2007, these four clinics saw 8,528 patients between the ages of 0 and 3 years and 3,065 patients between the ages of 4 and 5 years. Two of the four clinics will have the ASD modules turned on; two will not and will function as the control group. This will allow us to test the impact of the specific ASD modules above that of CHICA alone. The four clinics will be ranked by their size, where size is defined by the number of physicians and residents in the clinic. A randomization plan will be used such that the first and last ranked clinics will be assigned, at random, to one group (intervention or control) and the other two clinics will be assigned to the other group.

Although randomization at the physician/patient level is sample-size efficient, we chose a cluster randomization by clinic because contamination is a major concern. If we randomize at the physician level, physicians in the same clinic who are assigned to different treatment arms might communicate regarding the CHICA system in terms of its operation and consequences, which could contaminate the control arm. If we randomize at the patient level, the on and off usage of the CHICA might confuse the physician and lead some to think that CHICA is malfunctioning. Anecdotally, this has been our experience with the asthma and maternal depression studies we have conducted. We have found previously that randomization at the patient level can lead to irritation and inconvenience for both physicians and clinic staff. The limitation of randomization at the clinic level is inflated sample size and potential bias caused by unknown characteristics that are differentially distributed in the four clinics and related to the outcome. Characteristics of this nature could include awareness of ASDs by physicians, socio-economic status of patients and so on. To our knowledge however, there is no reported significance and scale of the effect of these factors. After weighing the limitation and advantage of each option, we decide to allocate two clinics to each of the study arms. We will adjust for intra-cluster correlation and potential confounders in the analysis.

### **D.1 Expand and modify an existing computer-based decision support system (CHICA) to assist pediatricians with identification and management of ASDs through the addition of the ASD screening and surveillance module and the ASD care and management module. (Aim 1):**

The CHICA system has been a successful prototype in the academic setting. Several enhancements are needed, however, in order to incorporate it into everyday use in pediatric office practices. Some of these are technical in implementation, some are functional. Many of our proposed changes are based on our experience, as reported in the literature (see section B.3); others arose during system development, clinic use, and evaluation, as we faced roadblocks in implementation, or when we recognized new potential applications. Other ideas came from users who were either unhappy with some component of the system or identified new areas where CHICA could be improved. Maximizing CHICA's utility will increase its impact on child health and enable the Autism diagnosis and treatment parameters to be added to the system. Enhancements will be completed in the first year of the project.

#### **D.1.1 Program CHICA to automatically evaluate M-CHAT forms**

One of CHICA's greatest strengths is its ability to automate the collection and analysis of large amounts of data for physicians. In this case, we will use CHICA to score the forms related to ASD screening, diagnosis and management. For example, CHICA will generate the Modified Checklist for Autism in Toddlers (M-CHAT) form for parents to fill out at their child's 18 to 24 month visit. This form will then be scanned into CHICA, where it

will be automatically scored by the computer system. This information will then be given back to physicians on the provider worksheet along with recommendations for next steps in those children who screen positive for ASD. All data can be grouped by patient and analyzed longitudinally.

#### D.1.2 Program CHICA to include an algorithm to assist pediatricians in the early identification of ASDs

ARDEN rules will be generated to use all of the collected data to recommend care for each child in the intervention arm of the study. Specifically, we will take the American Academy of Pediatrics (AAP) algorithm that has been created for Autism surveillance and screening and generate CHICA rules, using methods already developed in previous work (C.2.1). The overall flow of the CHICA ASD surveillance and screening module that will be used in the intervention arm of the study is pictured in Figure 8.

[figure not shown]

**Figure 8. Flow of the CHICA ASD Surveillance and Screening Module**

#### D.1.3 Program CHICA to include management and treatment recommendations to guide pediatricians in the care of children with ASDs.

Rules will also be written to assist pediatricians in the management of children suspected of having an ASD. This includes rules for suggested referrals and scheduling of follow-up appointments. We will also create rules to oversee practice in general, remind physicians when patients have missed visits, and when forms have not been turned in. CHICA will also generate just-in-time forms when appropriate in order to continually evaluate behavioral progress in each participant and to provide educational materials aimed at parents. This will

provide data for both the evaluation of current care and for necessary changes in the care regimen that may improve care. Specific components of the ASD care and management module is further described in section D.3.

#### D.1.4 Validation of the CHICA ASD modules

All CHICA rules and rule sets undergo thorough testing. We will first review the logic behind them in groups, to make sure that they appear valid. We will then proceed to simulations, running them with test patients to make sure that they are firing accurately. The final ASD rule set will be reviewed first by our investigators (pediatricians and a psychologist). Then the rule set will be reviewed by the Pediatrics Practice Advisory Committee (PPAC), a group of pediatricians in Indiana University Medical Group who develop and validate all practice guidelines for the participating community practices in the group. After rule deployment, we meet monthly with the CHICA User's Group, and review all CHICA process data in weekly team meetings to make sure that randomization and rule firing appears valid. Should any issues arise, we can implement fixes in a timely manner. This type of review goes on continuously and would be part of the study process as well.

#### D.1.5 Implementation of the CHICA system and ASD modules

We have extensive experience implementing the CHICA system and are aware of many potential barriers/pitfalls that can be encountered during deployment. Therefore we have developed a process to overcome these potential issues and to maximize the benefit of the technology. When we are ready to implement CHICA in the new sites, a technical team of lead programmers and pediatric informaticians will visit the clinic and conduct the following steps with members of the clinic, including physicians, nurses, clerical staff, and clinic leadership:

1. The CHICA system will be presented to the clinic.
2. With assistance from the CHICA team, the nursing and clerical staff will create workflow diagrams of the clinic, tracking flow of patients and medical records.
3. The CHICA team and the clinic staff will develop a plan for inserting CHICA into the workflow, including who will print forms, hand them to the patients, fill them out, and scan them into the system.
4. After CHICA is installed, the CHICA team will have a dry run – using the system without the clinic staff for one week to assure reliable technical function.
5. Clinic staff will receive a brief (<1 hour) training on how to fill out the forms and operate the scanner, as well as how to page CHICA staff if needed.
6. Clinicians will receive a 15-minute presentation about CHICA, how it works, and how to fill out forms.

We have (and will continue to have) one programmer who is always on call to perform technical support. In addition, a less technical member of the CHICA team will rotate full time through the clinics to assess CHICA's use and note any issues or problems for the full team to address. Further, we have established a CHICA user's group (CHUG), where the CHICA team leader ([name]) and one of the programmers meets in the clinics over breakfast or lunch on a regular schedule to allow clinic personnel to address members of the CHICA team. We have found that this installation and training package is sufficient to get CHICA up and running.

### **D.2 Evaluate the effect of the CHICA system ASD screening and surveillance module on the early identification of ASD in four pediatric practices (Aim 2).**

Through questions about ASD symptoms on the pre-screener form, we expect that patients with ASD will be more readily identified by the clinics with the CHICA ASD surveillance and screening module. This ASD module will also allow CHICA to prominently display messages on the physician worksheet. Our prior work has shown that these efforts are successful in helping the caregiver to identify patients who require attention.

#### D.2.1 Intervention Group:

The experimental intervention will include the enhanced version of the CHICA hardware and software, the CHICA ASD surveillance and screening module, and user support. Because the intervention is at the clinic level, all patients will be automatically cared for by the CHICA system and the CHICA ASD surveillance and screening module in the two intervention practices as part of routine medical care. The 2007 AAP surveillance and screening algorithm for ASDs addresses the care of children through the first 5 years of life. Therefore this is the target patient population for our intervention. The actual intervention will have a number of components that we expect will improve the surveillance and screening practices of pediatricians for ASDs:

- 1) *Case finding* – On the pre-screener form, parents will be asked simple questions in order to identify “red flags” that are indications for immediate evaluation (See Figure 8 Box 2). These include:
  - No babbling or pointing or other gesture by 12 months
  - No single words by 16 months
  - No 2-word spontaneous (not echolalic) phrases by 24 months
  - Loss of language or social skills at any age

Questions will also be asked to assess risk factors for ASD. These include:

- A sibling with ASD
- Parental concern
- Other caregiver concern
- Pediatrician concern

Each of these four risk factors is worth one point. If a child does not have a sibling with ASD and there are no concerns from the parent, caregivers, or pediatrician then a risk factor score of zero will be given. If the child has either a sibling with ASD or concern is expressed by a parent, caregiver, or pediatrician, then the child is given a risk factor score of 1. If the child has 2 or more risk factors then they receive a score of 2+ (See Figure 8). Based upon these concerns, screening might occur in the examination room. Screening would be done through the use of a printed M-CHAT form. These forms would be automatically scored by CHICA. Moreover, universal screening will occur at the 18- or 24-month visits through the use of an M-CHAT form printed at patient check-in. At these visits, all parents will be given a preprinted M-CHAT to fill out for their child in the waiting room (See Figure 8).

The M-CHAT is a simple screening tool that can be given to children during pediatric visits. It does not rely on the physician’s observation of the child, but on parents’ report of current skills and behaviors. The tool contains 23 yes-no items. Initial failure on the screener is defined as any three items failed, or any two critical items failed. The critical items were identified by discriminant function analysis of children with and without a disorder on the autism spectrum and included items concerning joint attention (proto-declarative pointing, bringing to show, following a point), interest in other children, responding to name, and imitation. The sensitivity is reported to be 87% and the specificity 99% in the referred sample (i.e., children already identified as having developmental concern). The M-CHAT was chosen due to its simplicity and the fact that it does not require physician administration.

The ASD surveillance and screening module will also allow CHICA to prominently display messages on the physician worksheet. Data that can be displayed on the physician worksheet includes whether parents have any Autism-related concerns about their child as identified on the pre-screener form and/or M-CHAT scores from universal screening that will occur at either the 18 or 24-month visit. Also if a child demonstrates a failure on the M-CHAT screener, follow-up questions would be displayed on the physician worksheet or via just-in-time documents to clarify and elicit specific examples of the child’s typical behavior relevant to each failed M-CHAT item.

- 2) *Diagnosis* – Because a positive screening result does not determine a diagnosis of ASD, any child who receives such a result must be referred for comprehensive ASD evaluation. Based on the child’s ability to refer for testing, this evaluation should include:
  - 3-generational family pedigree with health, developmental, and behavioral histories
  - Thorough physical exam with Wood’s lamp skin examination
  - Developmental and/or psychometric evaluation
  - Evaluation with standardized tools for presence of categorical DSM-IV-TR diagnoses
  - Assessment of parental knowledge of ASD and appropriate resources and skills
  - Laboratory investigation for etiologies or known coexisting conditions

Additionally, these children should also be referred to early intervention/early childhood education services (depending on the child’s age) and receive an audiologic evaluation. CHICA will make explicit recommendations to the physician on the physician worksheet to provide these referrals if appropriate and the system will also provide the proper forms so that such referrals and evaluation can be arranged (See Figure 8 Box 8).

- 3) *Reassessment* – CHICA will automatically track those who have been previously screened. According to the algorithm (See Figure 8), those who previously have been assessed should be automatically assessed at subsequent visits. CHICA can insure that participants are not lost to follow-up.

The overall flow of the CHICA ASD surveillance and screening module is pictured in Figure 8 and closely resembles the surveillance and screening algorithm for ASD recommended by the AAP.

#### D.2.2 Control Group

The two control clinics will also have the CHICA system in place and, therefore, all patients in the control clinics will be automatically cared for by the CHICA system. However, the CHICA system within the control clinics will *not* include the ASD surveillance and screening module. Instead, clinicians in these clinics will screen and diagnose children for ASDs using their standard methods of care. These control clinics will however receive paper copies of the 2007 AAP Surveillance and Screening Algorithm for ASDs.

#### D.2.3 Patient Recruitment and Consent

Four pediatric clinics in the IUMG-PC practice network will already be equipped with the CHICA system prior to the beginning of this research project. For this particular study, we will add the ASD surveillance and screening module to the CHICA system in two of these clinics (i.e., intervention clinics). The other two clinics will not be provided with the ASD surveillance and screening module (i.e., control clinics).

We will ask for a waiver of consent for this portion of the study as 1) there is little risk involved in supplying physicians with guidelines of care, 2) study procedures are within standards of usual care, 3) informing families that they may be part of an ASD study would bias their response to study questions and invalidate any and all results of the project, and 4) obtaining informed consent from the many thousands of patients who are seen at IUMG-PC clinics would be difficult and would itself create, because of the paperwork that would be required, a much higher risk of loss of patient confidentiality.

#### D.2.4 Data Collection

In order to evaluate the effect of the CHICA system on the screening and diagnosis of ASDs, data will be collected from two sources:

1. *Medical record abstraction.* We will use chart abstractions to assess each clinic's surveillance and screening practices related to ASDs. Research assistants (RAs) will be trained to review both the electronic medical record and paper charts for a variety of information including how often ASDs are screened for and how often surveillance is performed according to the 2007 AAP algorithm. To assess the reliability of chart abstraction, a random sample of 20% of the charts will be abstracted twice.
2. *Review of CHICA data.* Based upon information provided by physicians on the physician worksheet, CHICA will automatically collect data on the screening and diagnosis of ASD throughout the study period. Moreover, we can add questions to the pre-screener form to ask parents if their children have ever been diagnosed with an ASD.

Additionally, information about practice characteristics will be collected at baseline. The medical record abstraction and review of CHICA data will be conducted at baseline and at six-month intervals until study completion. These methods will allow a thorough description of the intervention's role in the process of ASD surveillance and screening.

#### D.2.5 Outcome Measures

The primary outcome of interest for aim 2 is the percent of children at the 18 or 24-month visits who are screened using an ASD specific screening tool (i.e., M-CHAT).

Data will also be gathered in order to look at the following secondary outcome measures:

- Percent of children under the age of 5 undergoing surveillance for ASDs (See Figure 8 Box 2)
- Percent of children where ASD surveillance led to screening with an ASD specific tool (i.e., M-CHAT)
- Percent of children who had a positive ASD screening result at the 18 or 24-month visit

- Percent of children who were referred for comprehensive ASD evaluation after positive ASD screening result
- Percent of children diagnosed with an ASD after completion of comprehensive ASD evaluation
- Percent of children referred appropriately to early intervention/early childhood education services after positive ASD screening result
- Percent of children referred for audiologic evaluation after positive ASD screening result.
- Mean and median age of children diagnosed with an ASD
- Percent of children re-screened appropriately based on AAP algorithm

Surveys will be administered at baseline and yearly to the entire staff of each practice, including physicians, clinical staff, administrative staff, and office managers in order to document how each practice is organized and provide detailed information about knowledge and attitudes about ASD screening, diagnosis, and management. Questions regarding knowledge and attitudes about ASD will be taken from the Autism Survey which is currently utilized by researchers with the HANDS in Autism Team at the Christian Sarkine Autism Treatment Center who are involved in this study. This survey was adapted from a previous survey instrument utilized by Stone. Staff will also be asked about their satisfaction with the CHICA system and the ASD modules.

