### **D.4 Sample Size (Aims 2 and 3)**

#### D.4.1. Sample Size Calculation for Aim 2

The primary outcome of interest for aim 2 is the proportion of children at the 18 or 24-month visits that will be screened for ASD using the M-CHAT in the intervention group and any ASD specific screening tool in the control group. Dosreis and colleagues found that while 82% of pediatricians reported screening for general developmental delays, only 8% screened for ASD. Though we do not anticipate much variability in this rate at our study clinics, we will use four different rates, 6%, 8%, 10% and 12%, at baseline to estimate intra-clinic correlation. This translates to an intra-class correlation coefficient 0.0041. However, for a conservative estimation of sample size, we will use intra-class correlation 0.0082, twice that of the correlation we estimated.

To be conservative, we will assume 10% of the children are screened for ASD under standard practice in our clinic sites. Based on pilot data involving a different universal screening tool in the pediatric population (i.e., the Ages and Stages Questionnaire), we expect at least 50% of the children at the 18 or 24-month visits will be screened in the intervention clinics. However, we will use a more conservative estimate, that is, 40% of the children will be screened using the M-CHAT.

Using a chi-square test and setting alpha at 0.05, the probability of detecting a statistically significant difference in the proportion of children screened at the 18 or 24-month visits between the intervention and the control group is 90% with an effective sample size of 49 per group. Hence, the total effective sample size ( $n^*$ ) is 98. The unit of randomization is the practice or clinic, but the unit of analysis is the individual patients. Since patients are nested within practice, responses from the patients within practice are likely to be correlated. This intra-cluster correlation must be taken into account in the calculation of sample size and in the analyses. We computed the number of patients per clinic,  $m$ , required for the study, using the following equation:

$$m = \frac{1 - \rho}{\frac{k}{n^*} - \rho}$$

where  $\rho$  = intra-practice correlation,  $k$  = number of clinics,  $mk$  = total sample size,  $n^*$  = total effective sample size =  $mk/DE$ , and  $DE$  = design effect =  $1 + \rho(m-1)$ 

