### **D.5 Data Analysis (Aims 2 and 3)**

For each of the two aims, baseline clinical and demographic data will be compared between the intervention and the control groups. Categorical variables will be examined using chi-square tests and continuous measures with Student's t-tests. The statistical analysis of the data will be performed using the SAS.

#### D.5.1. Data Analysis for Aim 2

The primary variable for aim 2 is whether a child at the 18 or 24-month visits was screened for ASD using the M-CHAT in the intervention group and any ASD specific screening tool in the control group. For this dichotomous outcome, we will use a non-linear mixed-effects model and will adjust for potential confounders (fixed effects) and clinic effects (random effects). To be specific, if  $Y_{ik}$  is a binary variable indicating whether the  $k^{\text{th}}$  patient in the  $i^{\text{th}}$  clinic was screened, we have

$$\log it(Y_{ik} = 1) = \alpha_i + \mathbf{X}_{ik}\boldsymbol{\beta}, \text{ where } \alpha_i \sim N(0, \varepsilon^2).$$

The random component  $\alpha_i$  correlates outcomes of patients cared by the same clinic. Physicians would not be considered as a nesting factor since the same patients at different visits may not be seen by the same physician. The vector  $\mathbf{X}_{ik}$  represents fixed covariates and  $\boldsymbol{\beta}$  represents the corresponding coefficients. The fixed covariates will include critical covariates such as treatment group, gender, and other patient and clinic level characteristics. We will also examine potential interaction terms among the covariates, particularly interactions between treatment arm and other covariates. If there is a significant treatment difference, we will report the 95% confidence interval of the treatment difference after adjusting for all confounding factors. The model will be fitted by the SAS procedure NLMIXED.

All secondary dichotomous outcomes, for example, whether a child under the age of 5 undergoes surveillance for ASDs, whether ASD surveillance led to diagnosis of ASD with an ASD specific screening tool and whether a child was referred for comprehensive ASD evaluation will also be analyzed using the same model as described above.

### D.5.2. Data Analysis for Aim 3

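### Five of the nine Aim 2 secondary outcomes are worded within groups that the screening module itself changes, and D.2.5 and D.5.1 do not settle on one denominator for the arm comparison.

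*Protocol*

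**What the plan says.** Protocol D.2.5 lists nine secondary outcomes for Aim 2. Five are worded within a group that forms only after care has begun:

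- Three are conditional on a positive screen: "Percent of children who were referred for comprehensive ASD evaluation after positive ASD screening result", and the matching items for early-intervention services and for audiology.
- One is conditional on a completed evaluation: "Percent of children diagnosed with an ASD after completion of comprehensive ASD evaluation".
- One is conditional on diagnosis: "Mean and median age of children diagnosed with an ASD".

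D.5.1 analyses all dichotomous secondary outcomes with the primary outcome's mixed logistic model, which compares arms. One of its examples is referral for comprehensive evaluation, given there with no positive-screen condition. Another is "whether ASD surveillance led to diagnosis of ASD with an ASD specific screening tool".

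The arms reach screening by different routes. Under D.2.1, every parent at the 18- or 24-month visit in an intervention clinic receives an M-CHAT. Under D.2.2, control clinicians follow their usual practice and hold the AAP algorithm on paper. For planning, D.4.1 says "we will assume 10% of the children are screened for ASD under standard practice in our clinic sites" and, for intervention, "40% of the children will be screened using the M-CHAT". In control clinics any ASD-specific tool counts as screening.

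**The concern.** The module works by changing who is screened, so it also changes who can screen positive, be evaluated or be diagnosed. The screen-positive children in the two arms may differ in number, in case mix and in the tool that identified them. Clinic randomisation balances the children who attend. It does not balance subgroups formed afterwards by the intervention.

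If D.2.5 is followed literally and the D.5.1 model is run among screen-positives, a module that leads to more referrals could look neutral or worse on the percentage referred. Age at diagnosis has the same weakness as a comparison, because finding children who would otherwise have been missed can raise the mean. Referral, diagnosis and age at diagnosis are the outcomes closest to Aim 2's goal of early identification, so a misleading contrast there would matter even with a sound primary analysis.

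**Working it through.** **The plan's own figure.** D.4.1 gives a sample size for the primary outcome only: "Using a chi-square test and setting alpha at 0.05", the power "is 90% with an effective sample size of 49 per group". For 10% v 40%, two-sided (sidedness is not stated):

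n = [1.960·√(2·0.25·0.75) + 1.282·√(0.10·0.90 + 0.40·0.60)]² / 0.30² = 41.7, so 42.

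The continuity correction raises this to 49, as stated. Then m = (1 − 0.0082)/(4/98 − 0.0082) = 30.4, so 31 per clinic. The figure reproduces, but no figure is given for any secondary outcome.

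**Inputs from the protocol.** Screening 40% v 10% and 3000 visits over three years (D.4.1); ASD prevalence 1 in 150 (D.4, Aim 3); M-CHAT sensitivity 87% and specificity 99%, reported for a referred sample (D.2.1).

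**Assumptions.** Visits split equally, 1500 per arm. The same test accuracy applies to whatever tool control clinics use. Intervention screening is unselected. Control screening reaches children with ASD E times as often as the overall control rate. Referral follows 95% of true and 50% of false positives. E and the referral rates are illustrative and do not come from the documents.

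**Positives per arm.** 1500/150 = 10 children with ASD per arm.

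- Intervention: 600 screened, 4 with ASD. True positives 4 × 0.87 = 3.48; false positives 596 × 0.01 = 5.96; total 9.44.
- Control, E = 1: 150 screened, 1 with ASD. 0.87 + 1.49 = 2.36.
- Control, E = 4: 150 screened, 4 with ASD. 3.48 + 1.46 = 4.94.

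**Same referral behaviour in both arms.**

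- Intervention: (3.48 × 0.95 + 5.96 × 0.50)/9.44 = 6.286/9.44 = 66.6%; over all children 6.286/1500 = 0.42%.
- Control, E = 4: (3.48 × 0.95 + 1.46 × 0.50)/4.94 = 4.036/4.94 = 81.7%; over all children 0.27%.

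| E (control) | Positives | Referred among positives | Referred among all |
|---|---|---|---|
| 1 | 2.36 | 66.6% | 0.10% |
| 2 | 3.22 | 74.3% | 0.16% |
| 4 | 4.94 | 81.7% | 0.27% |
| 6 | 6.66 | 85.3% | 0.38% |
| 8 | 8.38 | 87.4% | 0.49% |

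At E = 1 the arms agree. At E = 4 intervention shows a deficit of 15.1 points although behaviour is identical. With specificity assumed at 95% the E = 4 contrast is 64.5% v 54.7%, and at 90% it is 58.7% v 52.5%, so the artefact shrinks to 9.8 and then 6.2 points.

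**Better referral in intervention** (assumed 97% of true and 60% of false positives): (3.48 × 0.97 + 5.96 × 0.60)/9.44 = 6.952/9.44 = 73.6%; over all children 0.46%. Control exceeds 73.6% from about E = 2, so the conditional contrast reverses there although intervention refers more in both strata. Over all children intervention leads for E from 1 to 6. At E = 8 control leads, 0.49% v 0.46%, because it then screens 8 of the 10 children with ASD against 4. That would be a real difference in referrals, not an artefact of the denominator. These all-children figures count only referrals that follow a positive screen.

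**Age at diagnosis (hypothetical).** Control diagnoses 6 children at a mean of 36 months. Intervention diagnoses the same 6 at 33 months and 4 otherwise undiagnosed children at 44 months: (6 × 33 + 4 × 44)/10 = 37.4 months. The mean looks later although no child was diagnosed later.

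**Wording.** The D.5.1 phrase on surveillance leading to diagnosis corresponds to a D.2.5 item on surveillance leading to screening. D.2.1 states that a positive screen does not establish a diagnosis. The D.5.1 phrase is therefore inconsistent with both.

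**The case against.** The protocol never states denominators. D.5.1 names referral for evaluation with no positive-screen condition, under a model indexed by patient within clinic, which can be read as an analysis of all children. An SAP may settle it. This stands in part: it shows that the two sections do not give one denominator, and it rules out asserting that the arms will be compared only among positives.

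Four stronger readings are tempting, and the documents do not support them.

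- **That all the secondary outcomes are affected.** Surveillance under age 5 is not conditional, and a positive screen at the visit can be taken over all children there. Two others (surveillance leading to screening, appropriate re-screening) depend on an earlier care step but are less clear cases. Five of nine clearly fit.
- **That control children who are screened are mainly those with concerns.** D.2.2 says only usual care, with the algorithm on paper. Selectivity is a plausible inference from 10% discretionary screening, but without it the calculation gives no bias. D.2.1 also has the module prompting referrals, so a lower intervention referral rate cannot simply be assumed.
- **That the conditional models cannot be fitted.** Thirty-one per clinic is a minimum for the primary outcome, and D.4.1 expects 3000 visits. The counts above (about 9 v 2 to 8 positives) are sparse, not absent.
- **That age at diagnosis will be tested between arms.** D.5.1 assigns the model to dichotomous outcomes only, so no test is stated for age.

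It is also fair that follow-through after a positive screen is a legitimate process question. It should be kept, but not as a randomised comparison.

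**Conclusion.** The concern holds in a limited form. Five of nine Aim 2 secondary outcomes are worded within groups whose size and make-up the module alters. For the four dichotomous ones, D.5.1 plans an arm comparison without fixing the denominator. If they are analysed among screen-positive or evaluated children, the contrast is not protected by randomisation.

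The possible distortion of referral among positives ranges from none (unselective control screening) to about 15 points at an assumed fourfold enrichment with specificity 99%, and about 6 points at that enrichment with specificity 90%. Reversal is possible from about twofold enrichment under the assumed referral rates, but it is not shown. The size rests on assumed enrichment, referral rates and an equal split of visits. The denominator mismatch and the faulty D.5.1 phrase rest on no assumption. The primary outcome is unaffected.

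**What to change.** In D.2.5 and D.5.1:

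1. Make the between-arm analysis of each referral and diagnosis outcome over all children with an 18- or 24-month visit (or all under 5). Count any referral or diagnosis whether or not a screening tool was used. Requiring a positive screen would count control children referred on concern alone as failures and would partly repeat the primary outcome.
2. Report the percentages among screen-positive or evaluated children, and mean and median age at diagnosis, as descriptive follow-through measures without arm tests.
3. Where follow-up allows, add the cumulative proportion of all children diagnosed by fixed ages, censoring those who have not reached the age. Children seen late in a three-year study will not contribute to the later ages.
4. Correct the D.5.1 phrase so that surveillance leads to screening with an ASD-specific tool, matching D.2.5.

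The cost is mainly redrafting, but referrals made without a screen must be captured equally in both arms, and item 3 needs a defined cohort. Absolute percentages will be small (0.10% to 0.49% in the illustration), events will be sparse, and the follow-through question becomes descriptive.
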